### Sample size

In accordance with the recommendations for qualitative interviews [38–43], we estimated 25–30 participants for the workshops and focus groups. For each workshop day and focus group, eight to ten participants should be recruited. For the narrative interviews, which focus on in-depth content rather than quantity, we plan to recruit eight to twelve participants. In order to subsequently enable a sufficient Delphi process in which every person has their say, we will recruit twelve to 16 participants [44–46].

### Recruitment

We will primarily recruit participants for our study using a digital snowball principle. Therefore, a landing page was set up via the primary affiliation of the authors, on which all relevant study-information can be found (https://www.th-deg.de/sterneneltern). The university’s marketing service creates advertising materials. These will be distributed to relevant healthcare institutions via email or direct message with a request for forwarding. The study will also be publicized on social media (Facebook, Instagram, Twitter) via the university’s institutional channel. In addition, the aforementioned organizations will be asked to advertise the study on their own social media channels. In case of only a few participants being recruited via this approach, information material will be sent to midwife practices, birth centers, gynecologists, obstetrics departments in hospitals and support groups.

If a potential participant contacts the research team, an initial preliminary telephone interview takes place in which the intention of the study is explained. In addition, background information is queried and it is checked whether the participants actually correspond to the required eligibility criteria.

### Methodological framework of the study

The entire study is planned as a participatory research project and draws on the central premises and recommendations of Hartung et al. [47]. The aim is to organize the entire research process in a participatory manner, from reflecting on the current situation to identifying the research gap, formulating the aims and questions, designing the study and its methods, collecting and analyzing the data and publishing the results.

To this end, one participatory researcher ([name]) has been an integral part of the research team since the start of the study in March 2024 and is involved in all process steps and decisions, including this study protocol. The participatory researcher has no scientific training and works as a consultant for parents after stillbirth, being a mother of a stillborn child herself. She is encouraged to contribute her own experience and expertise from her work to the entire research process.

In addition to the joint agreements within the entire project team, the researchers also hold internal meetings to prepare and follow up on the discussions with the participatory researcher. The overarching concept of the project thus follows the understanding of participatory research, i.e. conducting studies not on, but with the people whose lived experience and living conditions are being researched [48].

In order to further emphasize the participatory approach and enable the research subject to be linked back to the affected group, this study also uses an experience-based co-design [38]. The aim of this approach is to better understand the experiences of those affected in order to improve healthcare and cooperation between HCPs. The focus is on those affected themselves and their families. In terms of implementation, this co-design is divided into two central phases: the 1) discovery phase and the 2) co-design phase.

In our study, after the general conception of the study with a participatory researcher, a comprehensive workshop with affected parents is planned (phase 1), in which the breadth of the topic and central aspects will be defined. The focus group interviews that take place at the end of the workshop are intended to reveal the needs and requirements of those affected. The results and missing data will then be considered in the subsequent narrative interviews (phase 2), which focus on the lived experience of parents during their loss. Provided that a sufficient number of participants can be recruited, no individuals who have already participated in the focus group interviews will be selected for the individual narrative interviews to avoid potential biases. Finally, recommendations will be developed from the entire data analysis and are to be agreed by affected parents within a Delphi survey (phase 3). This process ensures a continuous user-based development of a guideline for health professionals (phase 4), considering the experience, needs and requirements of those affected. The overarching methodological framework for our study and its phases are depicted in Fig. 1.

**Fig. 1 Fig1:**
[figure not shown]
Methodology of the study on parents after child loss

### Data collection methods

Based on the participatory, co-creative premise of this study, a workshop [40] will take place at the beginning of the research process, which will be repeated on a total of three days with different samples in Bavaria, Germany. As this study receives no financial support, we are unable to reimburse transportation expenses. Nevertheless, food, drinks and additional catering for the whole day will be provided on site. Eight to ten people per day who have lost a child themselves as a mother or father along the formulated inclusion criteria will take part in this workshop. The workshop is structured in three parts: 1) opening, 2) world café, and 3) focus group interview. In order to create a pleasant and trusting atmosphere, the researchers first introduce the study and themselves and then explain the general conditions of the day (dealing with each other, no right/wrong, everything remains in a protected space).

The participatory researcher will also be present throughout the workshop day as an additional contact person and confidant for the participants. Afterwards, the participants can tell their own story, if they wish. Thoughts, words and sentences from the participants are then collected on a large pinboard, which they formulate themselves in response to the question ‘What comes to your mind when you think back to the loss of your child?’. This session serves as a warm-up and brainstorming session. Participants should familiarize themselves with the associations of others and thus be stimulated in their own thinking.

#### World café

The participants are then divided into two small groups. Following the World Café method [49], which focuses primarily on the discussion among participants and the resulting thoughts and ideas, three stations are designed, each of which is attended by a small group for 30 minutes and moderated by researchers. The first station comprises the hierarchization of various needs and requirements of people identified in studies (e.g. communication, self-efficacy, safety). Two thematic scales (relevance, actual consideration) are laid out in the room; there is only a minimum and a maximum, but no fixed scaling. The small group should intuitively allocate the needs on this scale and justify what is placed where and for what reason. The researchers moderate this station and take field notes.

At the second station, the parents deal with public awareness of the phenomenon. Three short extracts from newspapers are used to present public narratives about parents after stillbirth or loss during birth, which the participants are then asked to assess critically. This is followed by questions about their own perception and identity: How is the topic of stillbirth currently debated in public? How do you want the loss of a child during pregnancy or birth to be covered in the media? The researchers again take on a moderating role and prepare field notes and audio recordings.

The third station addresses the ideal-typical care of affected families before and during the loss experience. A creative method is used here. In the first 20 minutes, the participants are given the opportunity to create a picture using the materials provided or to develop a poem or text. In the last 10 minutes, the developed artworks are then presented to the group. The researchers take photos of the results and field notes during the conclusive plenary presentation.

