### Problem definition

While much is known about the long-term effects of the loss of a child, a significant research gap is also evident at this point. Families express various needs during the intrauterine phase and their pregnancy loss (e.g. [21], ), but these are still not described and analyzed in a differentiated way. The experience before stillbirth (intrauterine phase) and during stillbirth (birth itself) is also not depicted in the literature, in contrast to the aftermath. This also means that there is a lack of explanations for the targeted development of interventions and the origin of long-term effects on the parents.

A closer look at international medical, midwifery and nursing literature also reveals that neither guidelines nor studies and textbooks contain recommendations on how to deal with parents during stillbirth. This is also evident in studies among healthcare professionals (HCPs). They often feel insecure when dealing with parents during stillbirth [22] and are confronted with the ambiguity of the situation in which they have to mediate between the parents and their needs on the one hand and the healthcare system, the facilities and their aims on the other [22]. Various challenges such as their own emotions and lack of knowledge influence the work of HCPs [23] and lead to parents being avoided and stigmatized [22].

HCPs state that they have little or no training in caring for this specific patient cohort [22]. They suffer during the care themselves [22] and experience stress, especially when they have little experience or knowledge and perceive the missed care or inadequate staff performance [24]. HCPs are longing for an in-depth understanding, multi-professional training and sensitization tailored specifically to this patient cohort [23].

This situation results in inadequate care for the parents. They feel poorly informed and have few opportunities to communicate with HCPs [25, 26]. Finding themselves in a highly challenging situation with special needs [27], parents often feel overlooked and experience indifferent or dismissive HCPs, which leads to anxiety and frustration [28]. These experiences along with the lack of interaction with HCPs shapes the parents not just temporarily, but for years [23, 26, 27].

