#### Focus groups

At the end of the workshop days, focus group interviews will be conducted in line with the methodological recommendations of Krueger [39]. These will last 60 to 90 minutes and focus on the needs and requirements of parents before and during the intrauterine or perinatal loss of their child. The focus group interviews serve to answer the second research question and provide a basis for the subsequent derivation of treatment recommendations.

Specifically, a semi-structured guideline is used for the focus group, which contains central topics, but is designed to enable a dynamic course of the interview and the addition of further topics. Starting with the introductory question about the general needs during the loss while pregnancy or birth, various core aspects (flow of information, the birth moment itself, expectations, handling strategies) are then addressed and concluded with a question about the ideal type of care. The interviews will be analyzed using Mayring’s qualitative content analysis [50] in the MAXQDA software.

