#### Delphi approach

Once the focus group interviews and narrative interviews have been analyzed, the research team will translate the findings into treatment recommendations. These are directed towards HCPs (physicians, nurses, therapists, midwives) who are involved in supporting and caring for parents before and during the intrauterine or perinatal loss of a child. The recommendations in the form of individual shorter or longer statements are to be agreed and further developed with affected parents in the sense of participatory, co-creative research. The Delphi method, which will be used as the final data collection instrument and represents the quantitative component of this mixed-methods study, is particularly suitable for this purpose.

Methodologically, a slightly modified form of the classic Delphi method is used [44–46]. Twelve to 16 affected parents are invited to the researchers’ university as experts to assess, evaluate and further develop the pre-formulated treatment recommendations in an iterative process over the course of a whole day. In preparation for this, the treatment recommendations will be sent to all participants two weeks in advance so that they can familiarize themselves with the formulations before the Delphi process. If necessary, several rounds will take place on the day itself. Each round consists of 1) appraisal, 2) discussion and 3) revision of the recommendations, and ends with a break.

In detail, the recommendations are to be evaluated anonymously via an online platform [51, 52]. This enables immediate visibility of the results and transparent mapping of the group’s assessment. After the assessment, the participants are free to briefly comment on the individual and controversial recommendations. The recommendations are then revised by the researchers on the basis of the discussion and put to the vote again. The aim is to achieve the greatest possible consensus or consensus over dissent [53], while adhering to the quality standards and criteria [54]. The Delphi rounds are repeated until this goal is achieved. If the time frame of a single session should prove to be insufficient, a follow-up date is to be agreed with the participants.

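### Every workshop parent ranks a literature list of needs before the focus group asks about needs, so for listed needs the plan cannot show what parents would have raised unprompted

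*Protocol article*

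**What the plan says.** The order of the day is fixed under Data collection methods: "The workshop is structured in three parts: 1) opening, 2) world café, and 3) focus group interview". In the opening, parents may tell their story and put their own words on a pinboard, in answer to a question about what the loss brings to mind.

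The World café section then describes three 30-minute stations for two small groups. At station 1 the material is supplied: "The first station comprises the hierarchization of various needs and requirements of people identified in studies", with communication, self-efficacy and safety as examples. The two scales are relevance and actual consideration, and the task is this: "The small group should intuitively allocate the needs on this scale and justify what is placed where and for what reason". On documentation the article says "The researchers moderate this station and take field notes". Audio recording is named for station 2 (public awareness and media) but not for station 1.

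The Focus groups section places the interview at the end of the workshop day, begins it with a general question on needs, and gives its purpose: "The focus group interviews serve to answer the second research question". The Problem definition says families express various needs, "but these are still not described and analyzed in a differentiated way".

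**The concern.** A focus group that is to establish what parents need should be able to separate what they bring from what they were handed. Here the participants have just sorted the researchers' own categories and defended each placement. An open question on the same subject later that day will draw partly on those categories, because they are fresh, already worded and already discussed by the group.

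What is at stake is how the answer to the second research question is read. If the focus groups return communication, self-efficacy and safety, a report could present this as independent confirmation of the literature when some of it echoes the station 1 cards. The focus groups are also a stated basis for the recommendations to professionals. The order cannot be undone once the workshops have been held.

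**Working it through.** There is no sample size, error rate or effect estimate to reproduce. The check is of sequence, exposure and what each record can show.

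**1. Sequence** (Data collection methods, World café, Focus groups)

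| Step | Prompt | Needs supplied or open? |
|---|---|---|
| Opening, pinboard | Associations with the loss | Open, but not about needs |
| World café, station 1 | Place and justify needs taken from studies | Supplied |
| World café, station 2 | Newspaper extracts, public debate | Not about care needs |
| World café, station 3 | Creative work on ideal care | Open, about care |
| Focus group | Opening question on general needs | Open, but after the list |

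No step asks for needs unaided before the list appears. Station 3 comes closest, but the article does not state the station order, so it may follow station 1.

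**2. Exposure.** Inputs: three workshop days and eight to ten people per day. Participants exposed before the focus group = 3 × 8 to 3 × 10 = 24 to 30, which is everyone. (The Sample size section gives 25–30 overall.) This assumes that both small groups visit all three stations; the rotation is not spelled out.

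**3. Interval.** Three stations × 30 minutes = 90 minutes of world café. If station 1 comes first, it ends 90 − 30 = 60 minutes before the café closes; if last, 0 minutes. The focus group is the next part of the day. The interval is therefore 0 to 60 minutes plus any breaks.

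**4. What can be inferred from a need mentioned in the focus group**

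| Need | Plan as described | With a written record before the list |
|---|---|---|
| Not on the list | Not supplied by the list, so identifiable as raised by parents | Same, and known whether it was already written down or is new |
| On the list, written by parents beforehand | Cannot be distinguished from the next row | Raised unprompted |
| On the list, not written beforehand | Cannot be distinguished from the row above | Possibly prompted; reported as such |

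The defect is confined to the second and third rows. The researchers hold the list, so the first row is safe already.

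**5. Other sources.** The narrative interviews are meant to use other parents if recruitment allows, so those parents would not have seen the list. However, these interviews are assigned to the first research question (experience), and their opening prompt concerns the loss. They can support the finding on needs indirectly but are not designed to answer it.

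**The case against.** The best defence is that the exercise is deliberate and suits the stated gap. The Problem definition does not say that needs are unknown; it says they have not been described in a differentiated way. Placing known needs by relevance and by actual consideration, with reasons, addresses that. Parents can put a listed need at the minimum, so the task can contradict the literature. The opening is meant to stimulate thinking, the focus group guide admits further topics, station 3 is free creative work, and the Delphi parents can develop the recommendations further. All of this stands as a reason to keep the ranking. It does not supply an unprompted statement of needs made before the list is seen.

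Several stronger readings are tempting, and the article does not support them:

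- *Supplied and parent-raised needs cannot be told apart at all.* They can be for every need that is not on the list.
- *No record of station 1 exists.* Field notes are planned. They are less complete than a recording, but they can hold the placements and reasons.
- *The missing audio is the cause.* A recording of parents discussing supplied cards would not show what they would have said without them. The article also names no recording method for the focus groups or interviews, so silence on audio is weak evidence, although the contrast with station 2 is explicit.
- *The recommendations leave out the world café.* The Delphi approach section says "Once the focus group interviews and narrative interviews have been analyzed, the research team will translate the findings into treatment recommendations". That sets the timing and excludes nothing. The methodological framework section speaks of the whole data analysis.

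**Conclusion.** The point holds in a limited form. On each workshop day every participant, 24 to 30 in all, ranks a supplied list of needs before the focus group that is to answer the second research question. For needs on that list the plan as described cannot show whether parents would have raised them unprompted, so agreement with the literature may partly reflect the list. Needs outside the list are unaffected by this ambiguity.

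Two limits apply. Exposure is total only if both small groups visit every station, which is the natural reading but is not spelled out. The direction of any bias is plausible, towards needs already in the literature, but its size cannot be derived from the article, and neither exposure counts nor minutes of talk measure it. This is a cheap improvement to be made before the workshops, not a flaw that invalidates the design.

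**What to change.** 1. **Ask first, show second.** Before the literature cards appear, have parents write down their own needs. Either use blank cards in the first 10 minutes of station 1, or add a second pinboard question on needs to the opening. The pinboard option has the advantage that both small groups answer before either has seen the list.
2. **Keep the ranking.** Place the parents' cards and the literature cards on the two scales together, mark which is which, and photograph the result.
3. **Tag by origin.** In MAXQDA give each need one or more of three attributes: raised before the list, on the supplied list, new in the focus group. Report these separately, so that a listed need written beforehand is distinguished from one that appears only after the cards.
4. **Secondary: audio-record station 1**, as is already done at station 2, to document the justifications. This does not itself remove priming.

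The focus group would still follow the list, so its own discussion remains primed. What the change adds is a prior record to compare it with.

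**Cost.** About 10 minutes of workshop time; if taken from station 1, 30 − 10 = 20 minutes remain for placing and justifying. Blank cards and one code attribute are trivial. If both groups visit station 1 on all three days, recording it adds 2 × 3 × 30 = 180 minutes of audio, some of which would need transcription in a study without funding. For that reason it ranks below steps 1 to 3.

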#### Focus groups

At the end of the workshop days, focus group interviews will be conducted in line with the methodological recommendations of Krueger [39]. These will last 60 to 90 minutes and focus on the needs and requirements of parents before and during the intrauterine or perinatal loss of their child. The focus group interviews serve to answer the second research question and provide a basis for the subsequent derivation of treatment recommendations.

Specifically, a semi-structured guideline is used for the focus group, which contains central topics, but is designed to enable a dynamic course of the interview and the addition of further topics. Starting with the introductory question about the general needs during the loss while pregnancy or birth, various core aspects (flow of information, the birth moment itself, expectations, handling strategies) are then addressed and concluded with a question about the ideal type of care. The interviews will be analyzed using Mayring’s qualitative content analysis [50] in the MAXQDA software.

